### Data management {19}

Data are stored in the following places:
FCHVs hold paper registers for menstrual monitoringInterviewers have lists of women enrolled in menstrual monitoring permanently stored on password-protected tablets, and survey data are temporarily stored before they are synchronised (encrypted) to a CommCare cloud server. Essential information required for case management is retained on the devices within the CommCare to facilitate follow-up and questionnaire flow.Enrolled women have a copy of some of their own data, recorded on their trial participant cardsHealth facilities are provided with enrolled women’s names and the IFA and albendazole prescribed by NAs.HERD International’s data management team in Kathmandu downloads all new data daily from the CommCare cloud server onto their server using a semi-automated system to extract csv files, import them into Stata and run automated do files for data pseudonymising, labelling and recoding.

Pseudo-anonymised data are shared with other data team members as needed but the person-identifiable information is stored in separate encrypted files, which are not used day-to-day unless follow-up lists need to be generated or maintained by authorised team members. Follow-up lists and data collector performance outputs are uploaded to a shared folder for the field managers and data coordinators to perform their checks.

All data are stored on password-protected, encrypted, secure server computers in lockable rooms at the Kathmandu office. Data on physical servers are backed up daily onto secure cloud servers and copied onto external secure backup hardware-encrypted hard drives in Kathmandu each week. The pseudonymised files are shared with named analysts / data managers for inspecting data quality and generating data summaries for the Data Management Committee and Trial Steering Committee as appropriate. Study arm is encoded but not labelled. Once all of the data have been collected and uploaded to the secure server and follow-up is complete, the data are deleted from supervisors’ laptops and data collection tablets, and eventually from the CommCare server.

Qualitative data collected in Awadhi and Nepali languages are transcribed in Nepali. After transcription, qualitative data collectors send audio recording and transcriptions to the HERD Kathmandu office where core team members check completeness and anonymisation and store the data in a lockable cabinet. The transcribed anonymised data is then translated to English, cross-checked with the original Nepali transcripts and thematically analysed.

#### Data cleaning

Data cleaning is completed by HERD International Data Management teams, NS and HHF as required. Variable naming, labelling and initial recoding is automated at the time of downloading. For all outcomes and important process variables and covariates, variable distributions are checked for normality and skewness and outliers identified and removed as necessary.

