##### Anaemia screening and tailored iron-folic acid therapy

At each home visit, following the nutrition counselling, the NA will measure the PW’s haemoglobin concentration using a hand-held Hemocue Hb 301+ analyser, measure her mid-upper arm circumference (MUAC) with a SECA tape (93/42/EEC) to assess thinness, and explain the results. Following GoN guidelines, the NA will advise the PW to take IFA as follows:
Not anaemic (Hb ≥ =11 g/dL), one IFA tablet (60 mg elemental iron and 400 μg folic acid) per day.Mildly or moderately anaemic (Hb 7–10.9 g/dL), two IFA tablets (120 mg elemental iron and 800 μg folic acid) per day.Severely anaemic (Hb < 7 g/dL), the NA will immediately refer the PW for a blood transfusion at a higher health facility.

At visit 1 (at 12 to 21 weeks’ gestation), the NA will provide sufficient IFA tablets for a period of 4–10 weeks until her second visit, at 22 to 26 weeks’ gestation. For all women, NAs will emphasise the importance of increasing dietary diversity and consuming micronutrient-rich food. For women with low (< 230 mm) or very low (< 210 mm) MUAC, the NA will also emphasise the importance of consuming additional calories through more frequent and/or larger meals and taking adequate rest. For women with MUAC ≥ 300 mm, the NA will stress the importance of keeping active during pregnancy and avoiding sugary or fatty foods and large portions of rice.

After repeating the haemoglobin and MUAC measurements at the second visit, the NA will explain to the woman how her anaemia and thinness status have changed and provide the appropriate IFA dose. She will also assess compliance to IFA by asking the PW about their tablet consumption and checking used blister packs. At visit 2, the NA will provide a single (400 mg) albendazole tablet if the PW has not already received it as per Nepal’s national protocol for women in their second trimester.

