#### Electronic data collection

Questionnaires are programmed in Nepali, Awadhi and English on android operating system tablets or mobile phones using the CommCare electronic data collection platform [92]. In-built jump-sequences and value limits prevent entry of data outside plausible ranges.

To enable seamless merging of data by participant and efficient case management and follow-up, unique identifiers (IDs) encoded into Quick Response (QR) codes are printed onto stickers. These are allocated to women enrolled by attaching them next to their names in menstrual monitoring registers. When a woman is enrolled in the trial, her QR code is attached to her a trial participant card (TPC) and to a trial participant list held by each interviewer. Her ID is scanned at every interaction with interviewers, dietary interviewers and NAs, enabling information stored in CommCare about that woman (such as name, LMP, and other details) to be ‘called up’ and used to ensure questionnaire flow and accuracy.

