## Statistical methods

### Statistical methods for primary and secondary outcomes {20a}

A detailed Statistical Analysis Plan, drawn up by the trial statistician (AC) and Nepal principal investigator (NS), will detail the analysis strategies, covariate adjustment and the approach to any missing data. Each version is presented to the Data Monitoring Committee (DMC) and Trial Steering Committee (TSC) for approval and the first version is prepared before the first patient is recruited.

Primary analysis is by intention-to-treat and will use the standard 5% significance level. Analysis of the primary outcome (haemoglobin concentration at the 30 ± 2 weeks) is based on linear regression, with random effects to adjust for clustering. Analyses are conducted with and without adjustment for predictors of the primary outcome (Table 4) including socioeconomic status, parity, age of PW, gestational age at measurement, maternal education and characteristics used in the restricted randomisation (individual level religion, ethnicity and travel time to the nearest health facility and cluster-level number of eligible women from the pre-trial census).

**Table 4 Tab4:** Variables to adjust for or to use in subgroup analyses and exposure variables

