Analysis of secondary and impact pathway outcomes (Table 1) and of process indicators (reported in 1 or more separate publications (Table 2)) will follow a similar methodology. We will use linear regression for continuous outcomes, logistic regression for binary outcomes, ordinal logistic regression for ordinal outcomes and negative binomial regression for ‘count’ outcomes such as number of IFA consumed. For continuous and count outcomes, before analysis of intervention effectiveness, the distribution will be examined and in the event of skewed or heaped data transformations such as log will be considered, or methods will be adapted such as for zero-inflation. For energy, iron and other micronutrients, which are (almost) ubiquitously consumed, we will use our duplicate measure to account for the wide intra-individual variability with a nonlinear random effects model and person-specific random effects (the National Cancer Institute method). For intakes of recommended foods that are only episodically consumed but also have wide within-person variance, we use a two-part model where the probability of consumption is estimated using a multilevel logistic regression, the amount consumed on consumption days is estimated by fitting a multilevel nonlinear regression model and the error terms of the two parts are correlated [108].

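### The data-cleaning rule removes outliers from every outcome, including primary haemoglobin, without limiting removal to errors or requiring it to be blind to arm

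*Protocol article*

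**What the plan says.** The Data cleaning section states its scope as "For all outcomes and important process variables and covariates" and then, after a check of each distribution for normality and skewness, the action: "outliers identified and removed as necessary". Table 1 makes Hb at 30 ± 2 weeks the primary outcome. Table 4 and the text after it make enrolment Hb a covariate in the primary model, so the rule reaches both.

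Four other places bear on it:

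- Electronic data collection: the form's "value limits prevent entry of data outside plausible ranges".
- Statistical methods, on skewed continuous and count outcomes: "in the event of skewed or heaped data transformations such as log will be considered, or methods will be adapted such as for zero-inflation". Deletion is not mentioned there.
- Statistical methods: "Primary analysis is by intention-to-treat and will use the standard 5% significance level".
- Data management: in the files shared with analysts, study arm is coded without a label.

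No section withdraws the removal rule or narrows it to errors.

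**The concern.** The sentence links a check of distributional shape to deletion. An unusual value is not necessarily a wrong one. The form already blocks implausible entries, so a good share of what still looks extreme at cleaning may be real. The intervention section itself treats very low Hb as a true state: "Severely anaemic (Hb < 7 g/dL), the NA will immediately refer the PW".

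Trimming on the outcome is not neutral when the arms differ. If the intervention raises Hb, a cut-off set on the pooled data removes more low values from control and more high values from intervention. Both push the estimate toward zero. The missing-data section counts an outcome as missing when the woman is unavailable or has moved away, so values deleted at cleaning are a further source of missing outcomes that it does not describe. Deleting an enrolment Hb value would likewise leave that woman without a covariate the primary model uses.

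The words *as necessary* leave the choice to whoever cleans the data. In an open trial that choice should be fixed in advance and made without the arm.

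**Working it through.** **Inputs from the protocol (Sample size, Table 3).** Difference 0.4 g/dL, SD 1.2 or 1.25, ICC 0.09, CV of cluster size 0.27, 27 clusters per arm, m = 15.6 or 10.4 outcomes per cluster, two-sided 5%.

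**Assumptions, not in the protocol.** Control mean Hb 10.8, the shape of the Hb distribution, the pattern of benefit, and the outlier rule itself.

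**1. The plan's own power.** Let L = m·ICC/(m·ICC + 1 − ICC) and DE = [1 + (m − 1)·ICC]/[1 − CV²·L(1 − L)].

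- For m = 15.6: L = 1.404/2.314 = 0.607; DE = 2.314/(1 − 0.0729 × 0.2386) = 2.355.
- Effective n per arm = 27 × 15.6/2.355 = 178.9; SE = 1.2 × √(2/178.9) = 0.127.
- Power = Φ(0.4/0.1269 − 1.96) = 88.3%.

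The other three cells come out at 85.7%, 82.1% and 79.0%. Table 3 reproduces, so its inputs are a sound base.

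**2. Normal Hb, uniform shift, common SD 1.2.** Control mean 10.8, intervention mean 11.2, pooled mean 11.0, pooled SD = √(1.2² + 0.2²) = 1.217. The mean of a normal truncated at standardised limits a and b is μ + σ[φ(a) − φ(b)]/[Φ(b) − Φ(a)].

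- *3 SD rule:* limits 7.35 and 14.65. In control a = −2.875, b = 3.208, and the mean rises by 1.2 × (0.00640 − 0.00232)/0.9973 = 0.0049. By symmetry the intervention mean falls by the same amount. Difference = 0.40 − 0.0098 = 0.390.
- *1.5 × IQR rule:* limits 7.72 and 14.28. In control a = −2.569, b = 2.902, and the mean rises by 1.2 × (0.01472 − 0.00591)/0.9930 = 0.0106. Difference = 0.379.

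Low values deleted per 421 women, control against intervention: 0.9 against 0.3 (3 SD) and 2.1 against 0.8 (1.5 × IQR).

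**3. Other shapes (simulation, 1,000,000 per arm, true difference 0.40).** The left-skewed mixture is 10% from a normal with mean 8.9 and SD 1.3, and 90% from a normal with mean 11.0 and SD 0.98. The skew-normal has shape −3.

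| Hb shape and benefit | 3 SD | 1.5 × IQR |
|---|---|---|
| Normal, uniform shift | 0.39 | 0.38 |
| Skew-normal, uniform shift | 0.38 | 0.37 |
| Left-skewed mixture, uniform shift | 0.38 | 0.36 |
| Normal, gain proportional to deficit below 12.5 | 0.38 | 0.36 |
| Left-skewed mixture, gain proportional to deficit below 12.5 | 0.34 | 0.30 |

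In the last row the low values deleted per 421 women are about 8 in control against 1 in intervention (3 SD), and about 17 against 4 (1.5 × IQR). A 2 SD rule gives 0.31 in the first row and 0.28 in the last.

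**4. Power and type I error.** Simulation of 54 clusters with normal Hb and a uniform shift, 4,000 runs, *t* test on cluster means:

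| Rule | Power | Type I error |
|---|---|---|
| None | 85.8% | 5.4% |
| 3 SD | 85.7% | 5.2% |
| 1.5 × IQR | 84.9% | 5.1% |
| 2 SD | 81.7% | 5.1% |

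Power moves little because trimming also lowers the SD. The harm falls mainly on the estimate.

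**The case against.** The strongest reply is that this is one generic sentence about cleaning. *As necessary* may mean only errors. Entry limits work on single fields: they miss within-range mistakes such as transposed digits or the wrong participant scanned, and they cannot screen nutrient intakes calculated after entry. So some cleaning is needed, and it does not follow that whatever survives the limits is genuine. That stands, but the sentence as written does not confine removal to errors.

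Safeguards exist. The arm is coded without a label in shared files, corrections to form problems are made reversibly in code, and analysis code and participant data are to be shared. These make removal traceable and partly masked. They are only partial: the coded arm remains in the file, staff are not blinded, and the cleaning section does not require the decision to be made without it.

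A SAP may define outliers. The missing threshold is therefore not the complaint. The complaint is that the protocol already fixes removal for all outcomes.

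Three stronger readings are tempting, and the documents do not support them:

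- *The effect could be roughly halved.* That needs marked skew and an intervention closing about 84% of each woman's deficit below 11, which pulls the intervention-arm SD to about 0.67 against the plan's 1.2 or 1.25.
- *The deleted women are chiefly the severely anaemic.* In the left-skewed mixture about 3 of 421 controls are below 7 g/dL (0.72%), while a 1.5 × IQR rule deletes about 12 to 17 low control values. Most lie above 7.
- *The rule directly contradicts intention-to-treat.* The protocol defines that as analysis as randomised regardless of uptake. Deletion creates a missing value and reassigns nobody, so the tension is loose.

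**Conclusion.** The point holds as a defect in a stated rule. As written, it permits removal of genuine primary-outcome values with no tie to error and no masking requirement. In every scenario examined the estimate moved toward zero.

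Under the plan's common SD and a uniform shift, 0.40 becomes about 0.37–0.39 g/dL with the usual rules, or 0.36 in one left-skewed variant. With left-skewed Hb and a gain weighted to low values it becomes about 0.30–0.34. That second case lowers the intervention-arm SD to about 0.93, so it also departs from the plan's common SD, though moderately. All sizes rest on an assumed Hb distribution and an outlier rule that the document does not supply.

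This is not a type I error problem if the rule is symmetric and applied blind, and the loss of power is modest. The case for change is an avoidable bias and open discretion over the primary outcome, set against a near-free remedy.

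**What to change.** Replace the removal clause in Data cleaning, and carry the same wording into the SAP:

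- An outcome value is corrected or set to missing only for a documented measurement or entry error, or if it lies outside physiological or device limits written down before data lock.
- The decision is made on a file with the arm code removed, and the number of values changed or blanked is reported by arm for each outcome.
- All other values stay in the primary analysis.
- Skewness is handled by transformation or an adapted model, as the statistical methods section already provides.
- Any analysis excluding outliers is a sensitivity analysis only, with its rule stated in advance.

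The same restriction should cover enrolment Hb. The cost is a sentence or two in each document and a short log at cleaning. Sample size, data collection and the primary model are unchanged.

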#### Data archiving

After the trial is complete, the pseudonymised trial master file, including all datasets, is securely stored electronically with trial partners in HERD, UCL and LSHTM. Both pseudonymised and person-identifiable data are uploaded to the UCL Data Safe Haven along with the questionnaires, data codebook and brief description of the trial. Archiving of data in Nepal follows HERD International’s and NHRC policies.

The pseudonymised data will be made open access using the UCL data sharing platform or similar as per MRC guidelines. Any request for archived person-identifiable data will go through the trial management team.

### Confidentiality {27}

It is necessary to obtain and maintain lists of participants’ names to enable women to be followed-up to detect pregnancy and track their progress through pregnancy. It is also necessary to communicate to local and health facilities women’s receipt of IFA and deworming at home visits, to prevent double dosing. However, person-identifiable information (names of household members and GPS location) will only be retained by the field staff who need to seek to interact with trial participants and this information will not be made available to others. Apart from follow-up lists, which interviewers and home visitors will utilise, all other data stored on portable, or team members’ computers are anonymised such that the participants are identified by their unique ID number but not their name, address or geolocation.

Person-identifiable information associated with trial participants such as their name and geolocation and signed consent forms are stored in separate encrypted data files in a UCL data safe haven and on encrypted and password-protected external media which are stored in locked cupboards kept by the trial PIs and data manager in HERD.

During the consent process, study participants are assured that all person-identifiable information will not be attached to the data used for analysis. They are also assured that the information they share with FCHVs regarding their menstrual or pregnancy status and any details recorded on data forms will not be shared with anyone in the community. Participants consent to their names and contact details being kept on follow-up lists on phones, tablets, computers, registers and paper lists but that this information are accessible only to specified members of the data management team and to the field team members that need to visit them during follow-up. They are told that the details of any IFA and deworming provided to them are shared with local health facilities to avoid double dosing. They understand that they will not be identifiable in the data that is used for the study analysis or in any data shared within and beyond the study team.

If a participant withdraws from the study after data are anonymised and shared for analysis, it may not be possible to remove their data, but we can assure them that they can be removed from follow-up lists in the future, if they do not wish to be contacted.

### Plans for collection, laboratory evaluation and storage of biological specimens for genetic or molecular analysis in this trial/future use {33}

No storable biological specimens are collected during this study.

## Statistical methods

### Statistical methods for primary and secondary outcomes {20a}

A detailed Statistical Analysis Plan, drawn up by the trial statistician (AC) and Nepal principal investigator (NS), will detail the analysis strategies, covariate adjustment and the approach to any missing data. Each version is presented to the Data Monitoring Committee (DMC) and Trial Steering Committee (TSC) for approval and the first version is prepared before the first patient is recruited.

Primary analysis is by intention-to-treat and will use the standard 5% significance level. Analysis of the primary outcome (haemoglobin concentration at the 30 ± 2 weeks) is based on linear regression, with random effects to adjust for clustering. Analyses are conducted with and without adjustment for predictors of the primary outcome (Table 4) including socioeconomic status, parity, age of PW, gestational age at measurement, maternal education and characteristics used in the restricted randomisation (individual level religion, ethnicity and travel time to the nearest health facility and cluster-level number of eligible women from the pre-trial census).

**Table 4 Tab4:** Variables to adjust for or to use in subgroup analyses and exposure variables

**Confounders/covariates to adjust for in analyses:**	
Wealth score constructed out of household assets	
Education status of pregnant woman (none, primary, secondary, higher secondary +)	
Parity (*n*)	
Age of pregnant woman in years	
Gestational age at measurement in weeks	
Baseline (study enrolment) measure of Hb (for primary outcome analysis)	
**Adjustments for study design**	
Religion (Muslim versus Hindu)	
Ethnicity (hills versus plains)	
Travel time to health facility	
Cluster size (number of eligible women identified in the cluster during the census as used during constrained randomisation)	
Cluster (as random effect)	
**Variables to use in subgroup analyses**	
Baseline (study enrolment) anaemia status	
Categories of BMI at enrolment (kg/m^2^)	
Wealth categories constructed out of household assets	
**Main exposure (independent) variable for analyses of outcomes above:**	
Study arm: Home visiting +PLA versus Control (which is the reference group)	
**Within the intervention arm the levels of exposure to PLA women’s groups and home visits are coded in three (independent) variables for analyses of a dose-response effect upon the outcomes above (or a subset of them):**	
Exposure to women’s group—score of exposure constructed out of number of meetings attended by pregnant woman and number attended by family members	
Exposure to home visiting with tailored counselling and dose of iron-folic acid supplements—score of exposure constructed out of number of meetings attended by pregnant woman and number attended by family members	
IFA consumption during pregnancy (count or ordinal score constructed from the count)	

Our primary analysis will also adjust for haemoglobin at enrolment, to gain precision, but we acknowledge the trade-off that this may dilute intervention effects since in principle cluster-level intervention effects could be mediated through haemoglobin at enrolment. In a sensitivity analysis, we will remove adjustment for haemoglobin at enrolment.

Analysis of secondary and impact pathway outcomes (Table 1) and of process indicators (reported in 1 or more separate publications (Table 2)) will follow a similar methodology. We will use linear regression for continuous outcomes, logistic regression for binary outcomes, ordinal logistic regression for ordinal outcomes and negative binomial regression for ‘count’ outcomes such as number of IFA consumed. For continuous and count outcomes, before analysis of intervention effectiveness, the distribution will be examined and in the event of skewed or heaped data transformations such as log will be considered, or methods will be adapted such as for zero-inflation. For energy, iron and other micronutrients, which are (almost) ubiquitously consumed, we will use our duplicate measure to account for the wide intra-individual variability with a nonlinear random effects model and person-specific random effects (the National Cancer Institute method). For intakes of recommended foods that are only episodically consumed but also have wide within-person variance, we use a two-part model where the probability of consumption is estimated using a multilevel logistic regression, the amount consumed on consumption days is estimated by fitting a multilevel nonlinear regression model and the error terms of the two parts are correlated [108].

